#### Modelling cost and EQ-5D data

Cost and EQ-5D will be analysed using generalised linear regression models and their extensions, to account for the non-normal distribution of the outcome, the presence of spikes in the distributions (eg, at zero for the costs and at one for the EQ-5D) and the role of baseline predictors. The regression outputs will inform the quantification of the cost-effectiveness model parameters, which will help predict the long-term mean cost and QALYs for the strategies being compared in the PROFID EHRA trial.

The costs and EQ-5D for the ‘Well’ state will be populated within the long-term CEA model using the value of their conditional predicted means from the regression analyses. The costs and EQ-5D associated with the occurrence of transient events will be calculated as cost increments or disutility associated with specific events.

### Prognostic variables

Based on feedback from clinical experts in the PROFID EHRA trial, the regression analyses for overall survival, costs and EQ-5D will consider the following prognostic variables as predictors: age at baseline, gender, race, LVEF, New York Heart Association class, history of atrial fibrillation, renal dysfunction, QRS interval, medically treated diabetes and history of MI.

Depending on the distribution of patients’ recruitment across centres and countries, the feasibility of a multilevel modelling approach to the regression analyses will be considered, to account for the hierarchical structure of individual-level data, which will be naturally nested within centres and countries.^49^ Missing outcome data in the PROFID EHRA trial, particularly in the resource use and EQ-5D, will be assessed and if necessary handled with appropriate strategies,^50^ such as a multiple imputation via chained equations approach.^51^

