### Within-trial cost-consequences analysis

Individual-level HRQoL and healthcare resource use data in the PROFID EHRA trial are collected via an electronic case report form which is completed at the baseline, 12-month and 24-month clinical visits.^38^ The CCA will provide information on HRQoL, healthcare resource use and associated costs for the two strategies being compared in the trial during the PROFID EHRA follow-up period. The average resource use consumption, total costs and EQ-5D will be summarised (alongside relevant measures of dispersion) at baseline (EQ-5D only) and at follow-up for the two treatment groups separately. The trial is not powered to detect statistically significant differences in costs and HRQoL—since the sample size calculation was based on overall survival as its primary outcome—and so no formal statistical testing for difference in the health economic outcomes between groups will be carried out in the CCA.^39 40^

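### The predictor list for the EQ-5D regression omits baseline EQ-5D, which the trial collects, so the post-trial utility estimates would be less precise than the data allow

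*Protocol article*

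**What the plan says.** The Protocol article deals with EQ-5D in four places.

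- **Collection** (Within-trial cost-consequences analysis): the form that records quality of life and resource use is "completed at the baseline, 12-month and 24-month clinical visits". A baseline score is therefore planned for each patient.
- **Predictors** (Prognostic variables): "the regression analyses for overall survival, costs and EQ-5D will consider the following prognostic variables as predictors: age at baseline, gender, race, LVEF", then "New York Heart Association class, history of atrial fibrillation, renal dysfunction, QRS interval, medically treated diabetes and history of MI". This is one list of ten variables for three different outcomes, introduced without 'such as' or 'including'. Baseline EQ-5D is not on it. No other section names it as a covariate, an offset or the base of a change score.
- **Model** (Modelling cost and EQ-5D data): generalised linear models and extensions are to allow for spikes "at zero for the costs and at one for the EQ-5D) and the role of baseline predictors". These predictors are not named there. The 'Well' state is then populated "using the value of their conditional predicted means from the regression analyses". The text does not say whether the EQ-5D model has a treatment term.
- **Within-trial summary** (Within-trial cost-consequences analysis, CCA): "EQ-5D will be summarised (alongside relevant measures of dispersion) at baseline (EQ-5D only) and at follow-up for the two treatment groups separately", and "no formal statistical testing for difference in the health economic outcomes between groups will be carried out in the CCA".

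Under Sensitivity analyses, the variance-covariance matrices of the regressions supply the parameter uncertainty for the probabilistic sensitivity analysis (PSA). A value of information analysis is also planned.

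**The concern.** The list appears to have been drawn up from clinical advice to serve survival, cost and EQ-5D together. The one predictor that belongs specifically to EQ-5D, the patient's own starting score, is not in it. All ten variables are demographic or clinical, and they stand in only partly for a patient's self-rated health at entry.

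If the regression is fitted with the list as it stands, variation that baseline EQ-5D would explain stays in the residual. The coefficients and predicted means are then less precise, the PSA is wider than the collected data require, and the value of information analysis may overstate what further research would add. In any one trial, part of that avoidable error is the chance difference in baseline EQ-5D between arms. If the model gives each arm its own 'Well' utility and holds it for life, that difference is multiplied over many years. The Discussion foresees a result with little or no mortality benefit, in which case incremental QALYs may be small and a few hundredths could matter.

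**Working it through.** **Stated figure.** The only relevant number in the article is the sample size of 3,595, randomised 1:1. It was set for all-cause mortality. The article does not give its inputs, so it cannot be reproduced here, and nothing below disputes it.

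**Inputs from the article:** N = 3,595, 1:1 allocation, discount rate 3.5%, threshold £20,000 to £30,000 per QALY.

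**Assumed inputs (the article gives none):** EQ-5D SD 0.25 (range 0.20 to 0.30); correlation ρ between baseline and follow-up EQ-5D 0.5 (range 0.4 to 0.7); duration of an arm difference 2 years, or 8 to 12 years.

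**1. Standard error of an unadjusted arm difference.** SE = SD × √(4/N) = 0.25 × √(4/3,595) = 0.0083 (0.0067 to 0.0100 over the SD range).

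**2. Gain from adjusting for baseline.** Adjusted variance = (1 − ρ²) × unadjusted variance.

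| ρ | Variance remaining | Variance cut | SE at SD 0.25 | Equivalent sample multiple |
|---|---|---|---|---|
| 0.4 | 0.84 | 16% | 0.0076 | 1.19 |
| 0.5 | 0.75 | 25% | 0.0072 | 1.33 |
| 0.6 | 0.64 | 36% | 0.0067 | 1.56 |
| 0.7 | 0.51 | 49% | 0.0060 | 1.96 |

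This compares with no covariates at all. Once the ten listed variables are in the model, ρ must be replaced by the partial correlation. If that were 0.3 to 0.5 (an assumption), the further cut would be 0.3² to 0.5², or 9% to 25%. The formula is exact for a linear model and approximate for other generalised linear models.

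**3. Chance baseline imbalance.** The 95% range is ±1.96 × 0.0083 = ±0.0163 (0.0131 to 0.0196 over the SD range). The part expected in the unadjusted follow-up difference is ρ × imbalance:
- at one SE: 0.5 × 0.0083 = 0.0042;
- at the 95% limit: 0.5 × 0.0163 = 0.0082 (0.0052 to 0.0137 over all SD and ρ values).

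**4. Simulation check.** In 4,000 simulated trials at N = 3,595 and ρ = 0.5, both estimators were unbiased on average. Their SDs, scaled to an EQ-5D SD of 0.25, were 0.0084 unadjusted and 0.0073 adjusted. Baseline imbalance correlated 0.50 with the unadjusted estimate and 0.01 with the adjusted one.

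**5. Lifetime effect, if the 'Well' utility differs by arm and the difference persists.** Discounted years = (1 − 1.035^−T)/ln(1.035).

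| T (years) | Discounted years | QALYs at 0.0082 | At £20,000 | At £30,000 |
|---|---|---|---|---|
| 2 | 1.93 | 0.016 | £317 | £475 |
| 8 | 6.99 | 0.057 | £1,147 | £1,720 |
| 12 | 9.83 | 0.081 | £1,612 | £2,419 |

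At one SE the 8- to 12-year figures are 0.0042 × 6.99 = 0.029 and 0.0042 × 9.83 = 0.041 QALY. Over all the assumed SD and ρ values, the 95% limit runs from 0.0052 × 6.99 = 0.036 to 0.0137 × 9.83 = 0.135 QALY. These are upper figures, because NYHA class and the other listed covariates would absorb part of the imbalance. If the 'Well' utility is common to both arms, the direct carry-over is nil.

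**The case against.** The strongest reply is that the article never says baseline EQ-5D will be left out. The regressions will 'consider' the listed variables, the modelling section speaks generally of baseline predictors, and longitudinal data could bring the baseline score in as a repeated outcome. Nor is the list a complete model specification: it omits treatment arm as well. Read as exhaustive, it implies a common utility and no carry-over. Read as open, it does not exclude baseline EQ-5D. This stands against any claim that the plan rejects adjustment. It does not remove the point. The general phrase names no variable, while the section that does name them leaves out the obvious one.

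Three stronger readings are tempting, and the documents do not support them.

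- **Imbalance biases the QALY comparison.** Under randomisation, chance imbalance is part of the sampling error of the unadjusted estimate, which the PSA already carries. Imbalance and lost precision are one efficiency point, not two harms.
- **The error necessarily runs through lifetime QALYs.** That needs an arm-specific and lasting 'Well' utility, and the article states neither. The pre-trial model is unaffected, since it takes EQ-5D from an external register.
- **The CCA is distorted or deficient.** It is descriptive by design and shows EQ-5D "at baseline (EQ-5D only) and at follow-up for the two treatment groups separately", so an imbalance would be visible. It rules out formal testing, not estimates with intervals. A between-arm interval there is a reporting preference.

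It is also fair to say that SD, correlation and duration are all assumptions.

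**Conclusion.** The point holds as a matter of efficiency in the post-trial EQ-5D modelling. The one list of predictors given for that regression omits a variable that the trial collects and that usually predicts the outcome best. The avoidable variance in an arm difference is 16% to 49% of the unadjusted variance for an assumed correlation of 0.4 to 0.7, and less beside the ten listed covariates. There is no systematic bias.

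The effect on lifetime incremental QALYs is conditional. At the 95% limit, with SD 0.25 and correlation 0.5, it is about 0.06 to 0.08 QALY over 8 to 12 years, 0.016 over 2 years, and nil if both arms share one utility. The omission and the direction of the precision loss do not depend on the assumed values; the sizes do. It is a modest point, worth acting on because the remedy needs no new data.

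**What to change.** - In Prognostic variables, add baseline EQ-5D to the predictors of the EQ-5D regression, or state that baseline, 12-month and 24-month scores will be modelled jointly.
- Include baseline EQ-5D in the imputation model, if multiple imputation is used.
- State whether the 'Well' utility has a treatment term and, if so, how long the difference is assumed to last. When predicted means are formed, use the same baseline EQ-5D value or distribution for both arms.
- Optional: beside the CCA summaries, give a baseline-adjusted EQ-5D difference with a 95% confidence interval and no p-value. This is compatible with the decision not to test.

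The cost is a few sentences of analysis wording. No new data are needed. With 256 of 3,595 patients enrolled at 20 October 2025, the change can still be prespecified.

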### Incremental analysis

Comparison of the mean costs and mean QALYs associated with the strategy OMT with ICD vs the strategy OMT alone will be conducted using estimates from the long-term CEA model. An incremental cost-effectiveness ratio (ICER) will be calculated—if no strategy is found to be dominant^52^—to examine the additional costs required to achieve an additional QALY gain. In a budget-constrained healthcare system, having to pay additional costs to gain additional QALYs results in health lost somewhere else in the system, because funding one treatment necessarily shifts resources away from other uses, thereby forgoing their health benefits. In economic evaluation, the cost-effective treatment is therefore the one with the greatest health benefits, net of the health lost due to its costs. In practice, cost-effectiveness is assessed by comparing the ICER against a threshold whose value represents the rate at which the healthcare system improves health. Given the context of this evaluation is in the UK, where often policy decisions are made using the NICE threshold between £20 000/QALY and £30 000/QALY,^29^ we compare the ICER against this threshold as well as the cost-effectiveness threshold used by the Department of Health and Social Care in their impact assessments.^53 54^

### Subgroup analysis

If relevant, ICERs for different baseline risk profiles will be calculated to understand whether the ICD implantation with OMT can be more cost-effective for certain subgroups.^55 56^

### Sensitivity analyses

Sensitivity analyses will be conducted to explore the robustness of the study result with respect to the estimated uncertainties within the long-term CEA model. A one-way or multi-way sensitivity analysis will be performed on key deterministic parameters such as the discount rate and assumptions relating to the ICD device cost, device-related complications and the duration of treatment effects on overall mortality.

A probabilistic sensitivity analysis (PSA) will be conducted to reflect the sampling uncertainty in model parameter estimates using Monte Carlo simulation. The distributions of the model parameters (eg, transition probabilities or event rates, costs and EQ-5D) will be informed by the analysis of the trial data and external sources. The variance-covariance matrix for the sampling uncertainty of the parameters will be extracted from the regression models, and correlation between parameters in the regression models will be handled using the Cholesky decomposition method.^57^ A cost-effectiveness plane will be displayed to illustrate the distribution of incremental costs and incremental QALYs from the simulation. The results of the PSA will also be used to produce a cost-effectiveness acceptability curve to visualise the probability of cost-effectiveness across a range of cost-effectiveness thresholds.

Value of information analysis will be conducted to estimate the expected gain from reducing uncertainty through the collection of more information on key parameters and determine whether it is worth investing resources to obtain more information on these by funding further research in the future.^58 59^ Value of heterogeneity analysis will be performed to measure the gains from providing tailored recommendations across subgroups with current evidence and the value of future research to facilitate stratified treatment decisions.^60^

### Ethics and dissemination

The PROFID EHRA trial, under legal sponsorship of Charité—Universitätsmedizin Berlin, Germany, received its first ethics approval by the Medicine Research Ethics Committee of the La Paz University Hospital in Madrid, Spain (reference number LHS-2019-0209). Before including patients, for all participating study centres, the required local, central and/or national ethical approval has to be obtained. As of the date 13 November 2025, at least one participating study centre in the following countries has received ethical approvals from relevant ethics committees: Austria, Belgium, Czech Republic, Denmark, France, Germany, Great Britain, Hungary, Israel, the Netherlands, Poland and Spain. Results will be shared with the general public through various media channels and additionally with healthcare professionals and the scientific community through scientific meetings, conferences and publications.

## Discussion

The PROFID EHRA trial will reassess the effectiveness of ICD with OMT among post-MI patients with reduced LVEF, with a view to updating clinical guidance that is based on evidence from trials conducted more than two decades ago. The economic evaluation analysis proposed in this study will provide the cost and health implications of using OMT alone in place of ICD implantation on top of OMT, using existing evidence while the trial is ongoing and using the PROFID EHRA trial in combination with external sources on the availability of trial data.

The necessity of an economic evaluation in a non-inferiority trial might be questioned, especially if no mortality benefit is expected in the trial, and the health system can save money without compromising outcomes. However, conducting an economic evaluation in this scenario is still important for several reasons. First, the health effects and cost implications of ICD implantation can vary significantly among patients with different risk profiles.^55 56^ Understanding these variations can help develop tailored policy recommendations and ensure efficient resource allocation. Second, evidence from economic evaluation can provide comprehensive information about the magnitude of cost and benefit implications in the long term to support the implementation of policy changes. This includes not only direct short-term savings but also potential shifts in resource allocation in the longer term as patients’ earlier treatment pathway modifies their need for subsequent care. Lastly, the results of economic evaluation can reflect trade-offs that may be observed in the final results. For instance, even if the trial reveals slightly worse clinical outcomes but with significantly reduced costs, it may still be considered cost-effective as the cost savings can be invested by payers to support other forms of care in the system. The decision-makers will then need to trade off between the health losses in the clinical population in focus and the health gains achievable by freeing up resources to spend on other healthcare priorities. Thus, an economic evaluation is essential for informed, nuanced decision-making in non-inferiority trials such as PROFID EHRA.

This proposed economic evaluation focuses on ischaemic patients, in line with the inclusion criteria of the PROFID EHRA trial.^21^ Non-ischaemic cardiomyopathy is not considered as their risk stratification and potential benefit from ICD therapy has been studied in the Danish Study to Assess the Efficacy of ICDs in Patients with Non-ischemic Systolic Heart Failure on Mortality (DANISH) which found no significant reduction in long-term all-cause mortality of ICD implantation compared with OMT.^61^ As such, the findings from this study cannot be transferred to the non-ischaemic population, where the clinical and economic value of ICDs remains an important but distinct question.

One strength of this economic evaluation protocol is that it proposes an evidence-based iterative approach for evaluating the cost-effectiveness of ICD implantation for post-MI patients with reduced LVEF. The long-term model-based pre-trial CEA will provide evidence to support potential disinvestment decisions about the use of ICDs in the patient population defined by the PROFID EHRA trial and quantify the extent to which further research in this decision space is required. The within-trial CCA and long-term model-based post-trial CEA will benefit from the direct measurement of both health outcomes and resource use within the same study context, providing robust evidence for decision-making in an RCT setting instead of using data solely from external sources.

The limitations of this study are mainly attributed to uncertainties in model structure and model parameters. The proposed CEA model structure will consider two health states (ie, Alive and All-cause death), which differs from some previous published studies^62^,^67^ that considered specific causes of death in the CEA. The reason for not specifying the death causes in the proposed model is that the all-cause mortality is the primary endpoint of the PROFID EHRA trial,^21^ and it is preferred that the health states in the long-term CEA model align with the trial design. To reflect that the purpose of ICD implantation is to reduce risk of SCD, an additional model structure that includes both SCD and Death due to other causes will be considered in the sensitivity analysis upon the availability of trial data. The transient events are not assumed to structurally affect all-cause mortality, as the all-cause mortality for OMT alone and ICD+OMT will reflect the fact that some patients receiving ICD will experience complications and replacements which may result in death, and modelling their impacts on mortality may add unnecessary structural complexity and introduce the risk of double counting.^68^

In addition, for the pre-trial CEA, several model parameters will need to be derived from the published literature and/or experts’ opinion; and even for the post-trial CEA, given the limited trial observation period, some potentially important parameters will remain uncertain such as the duration of the treatment effect on mortality, long-term rates of device replacement, etc. The risk of complications related to ICD devices may vary by device type,^17^ and depending on data quality in the trial, the impact of choice of device will be explored using sensitivity analysis.

This economic evaluation applies an NHS and PSS perspective as recommended by NICE guidance in the UK,^29^ with a view to extending evaluation to the contexts of other participating countries in due course. We consider that the proposed model structure will generalise to other healthcare systems. However, the application of this economic evaluation protocol to other specific countries’ contexts may not be straightforward, depending on multiple factors including quantity and quality of the data collection in the country of interest, whether this country participated in the PROFID EHRA trial, as well as the normative framework for using economic evaluation studies to guide health policy decisions in each jurisdiction.

From a societal perspective,^69^ the indirect costs such as out-of-pocket and productivity losses, as well as the environmental impacts of device manufacturing, replacement and end-of-life disposal, may not affect both treatment strategies equally. While a societal perspective is beyond the scope of this evaluation study, an explicit consideration of these additional costs (and benefits) will be necessary to inform funding decisions in those jurisdictions that mandate a broader perspective than the one adopted in the UK.

In conclusion, this protocol outlines the economic evaluation methods to assess the value for money of using OMT alone in place of currently recommended treatment—ICD with OMT—among post-MI patients with reduced LVEF. Its findings will provide important and up-to-date insights for shaping policy decisions regarding the recommendation of ICD implantation in this patient population.
